### Composition of groups and randomization process

The volunteers will be randomly allocated to four experimental groups (n = 7 per group) based on the LLLT dose (phase 1) and power (phase 2) (Figure 1). Randomization will be carried out by a simple drawing of lots (A, B, C or D). The laser unit will emit the same sound regardless of the programmed power output. Randomization labels will be created using a randomization table at a central office, where a series of sealed, opaque, numbered envelopes will be used to ensure confidentiality. Randomization will be conducted by a participating researcher, who will have the function of programming the laser device based on the randomization results. This researcher will be instructed not to inform the participants or other researchers regarding the LLLT dose (phase 1) or power (phase 2) until the study has been completed. Thus, the researcher in charge of the administration of the LLLT will be blinded to the dose and power applied to the volunteers.

**Figure 1 F1:**
[figure not shown]
**Flowchart of design**, **composition of groups and protocols in phases 1 and 2.** MVC, maximum voluntary contraction.

### Experimental protocol

#### Evaluations and informative procedures

Evaluations will be carried out before and at the end of the isokinetic protocol by a researcher blinded to the LLLT dose (phase 1) and power (phase 2). The volunteers will then be informed about the procedures and will sign a statement of informed consent in compliance with Resolution 196/96 of the Brazilian National Board of Health prior to the execution of the study. All individuals in both phases will be submitted to the same evaluation protocol, which will involve the aspects described below.

#### Personal data

A questionnaire will be administered addressing age (years), body mass (kilograms), height (centimeters), dominant lower leg, schooling (no schooling, elementary school education, high school education, university education or postgraduate degree) and marital status (single, married or widowed).

#### Blood samples and biochemical analyses

Following the informative process and randomization, blood samples (10 ml) will be collected from the antecubital vein before and 1 minute after the eccentric contraction protocol. Blood samples will also be collected 1, 24, 48, 72 and 96 hours after the protocol. The samples will be taken by a nurse blinded to the allocation of the volunteers to the four experimental groups. One hour after collection, each sample will be centrifuged at 3,000 rpm for 20 minutes. Pipettes will be used to transfer the serum to Eppendorf® tubes (Eppendorf, Hamburg, Germany), which will be stored at −80°C until analysis.

Blood analysis will involve the determination of CK and lactate dehydrogenase (LDH) activity as indirect markers of muscle damage, using spectrophotometry and specific reagent kits (Labtest Diagnóstica, Lagoa Santa, MG, Brazil); IL-1β, IL-6 and TNF-α levels as inflammatory markers, using ELISA and specific reagents (R&D Systems, Minneapolis, MN, USA); and thiobarbituric acid reactive substances (TBARS), carbonylated proteins, catalase (CAT) and superoxide dismutase (SOD) as markers of oxidative stress, using spectrophotometry and specific reactions.

#### Evaluation of delayed onset muscle soreness (DOMS)

Delayed onset muscle soreness (DOMS) will be evaluated based on the pressure pain threshold, using an analog algometer (Baseline®, Rome, Italy). This device consists of a rod with a rounded rubber tip coupled to a pressure (force) meter. The display presents values in kilograms. As the surface of the rubber tip measures 1 cm^2^, the reading is expressed in kilograms per square centimeter (kg/cm^2^). Values range from 0 to 10 kg, with a precision of 0.1 kg. The most sensitive areas of the knee extensors (medial, lateral and central) of the non-dominant lower limb will be located through palpation by an examiner blinded to the allocation of the volunteers to the different groups and will be marked with a dermographic marker. The cylindrical end of the equipment will be positioned perpendicularly to the demarcated area. Pressure will be applied to the surface of the skin with a gradual increase in increments of 0.1 kg. The volunteers will be instructed to say ‘yes’ when the pressure exerted becomes painful. Three measures will be taken with the algometer on the same demarcated point of the aforementioned muscle sites. The mean pressure pain threshold will be determined from the three readings of each of the three sites and the mean values will be used in the statistical analysis. Readings will be taken prior to stretching and warm-up, 1 minute after the eccentric contraction protocol as well as 1, 24, 48, 72 and 96 hours after the execution of the protocol.

#### Stretching and warm-up

Prior to the isokinetic protocol, the volunteers will perform three 60-second sets of active stretching of the knee extensors of the non-dominant lower limb. The volunteers will then perform a warm-up exercise consisting of pedaling a stationary bike (Inbramed, Porto Alegre, RS, Brazil) at 100 rpm for 5 minutes without load.

#### Isokinetic protocol: maximum voluntary contraction (MVC)

An isometric dynamometer will be used for the evaluation of muscle function and the execution of the exercise protocol. This instrument is considered the method with the greatest reliability for the measure of the musculoskeletal performance. Immediately after the stretching and warm-up exercises, the maximum voluntary contraction (MVC) test will be performed. For such, the volunteers will sit on the seat of the isokinetic dynamometer (System 4, Biodex Medical Systems, Inc., Shirley, NY, USA) with an angle of 100° between the trunk and hip and the non-dominant leg positioned with the knee at 60° of flexion (0° corresponds to complete knee extension) and attached to the seat of the dynamometer by a strap. The dominant leg will be positioned at 100° of hip flexion and will also be attached to the seat by a strap. The volunteers will also be attached to the seat of the dynamometer through the use of two straps crossing the trunk. The volunteers will be instructed to cross their arms over the trunk and the axis of the dynamometer will be positioned parallel to the center of the knee. The MVC test will consist of three 5-second isometric contractions of the knee extensors of the non-dominant leg. The highest torque value of the three contractions (peak torque) will be used for the statistical analysis. The choice of this parameter is due to the fact that this variable reflects the maximum generation of force by the muscle. Instructions on how to execute the test will be given first and the volunteers will receive verbal encouragement during the execution of the test. This test has demonstrated reliability and reproducibility in a previous study carried out [28]. The MVC will be performed immediately (1 minute) after the eccentric contraction protocol as well as 1, 24, 48, 72 and 96 hours after the eccentric contraction protocol to evaluate post-exercise muscle recovery.

### Low-level laser therapy (LLLT)

#### Specifications

A five-diode cluster laser device (each cluster with 0.0364 cm^2^; wavelength: 810 nm; power: 0, 100, 200 or 400 mW in each diode; continuous light emission) (Thor Photomedicine, Chesham, UK) will be used for LLLT. The functioning of the laser will be verified prior to the treatment of each volunteer, with an inspection of the energy source, application points and energy measurement. To ensure blinding, the device will emit the same sounds regardless of the programmed mode (active or placebo).

#### Variation of dose (phase 1)

In phase 1, the output power will be fixed at 200 mW and LLLT will be applied 2 minutes prior to the pre-exercise MVC test with the cluster in direct contact with the skin at six distinct sites of the knee extensor musculature of the non-dominant limb (two medial, two lateral and two central sites). As the cluster has five diodes and six different sites will be irradiated, a total of 30 points will be irradiated in the musculature. Based on the results of the randomization, the volunteers of the four experimental groups will receive the following doses: Group A, 2 J per diode, 10 J on each application of the cluster with 200 mW (10 seconds of irradiation at each site), 60 J of total irradiated energy on the muscle (60 seconds of total irradiation time); Group B, 6 J per diode, 30 J on each application of the cluster with 200 mW (30 seconds of irradiation at each site), 180 J of total irradiated energy on the muscle (180 seconds of total irradiation time); Group C, 10 J per diode, 50 J on each application of the cluster with 200 mW (50 seconds of irradiation at each site), 300 J of total irradiated energy on the muscle (300 seconds of total irradiation time); and Group D, 0 J per diode (placebo) (20 seconds of irradiation at each site, 120 seconds of total time, but without effective irradiation).

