**Design and methods:**

A double-blind, randomized, placebo-controlled clinical trial with be conducted. After fulfilling the eligibility criteria, 28 high-performance athletes will be allocated to four groups of seven volunteers each. In phase 1, the laser power will be 200 mW and different doses will be tested: Group A (2 J), Group B (6 J), Group C (10 J) and Group D (0 J). In phase 2, the best dose obtained in phase 1 will be used with the same distribution of the volunteers, but with different powers: Group A (100 mW), Group B (200 mW), Group C (400 mW) and Group D (0 mW). The isokinetic test will be performed based on maximum voluntary contraction prior to the application of the laser and after the eccentric contraction protocol, which will also be performed using the isokinetic dynamometer. The following variables related to physical performance will be analyzed: peak torque/maximum voluntary contraction, delayed onset muscle soreness (algometer), biochemical markers of muscle damage, inflammation and oxidative stress.

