#### Variation of power (phase 2)

The aim of phase 2 is to determine the best power/irradiation time (Watts/s) for use on humans to enhance muscle recovery following physical exercise. For such, the dose with the best results in phase 1 will be used and the same methodological and evaluative measures will be employed. Thus, only the power of the equipment (and consequently irradiation time) will be varied (100, 200, 400 or 0 mW). As energy (E) expressed in Joules is equal to power (P) expressed in Watts multiplied by time (t) measured in seconds, different power variations will lead to the same total energy delivered to the tissue. *A priori*, if the best dose were determined to be 10 J, the following would be the parameters:

•10 J = 0.1 W (100 mW) × 100 s

•10 J = 0.2 W (200 mW) × 50 s

•10 J = 0.4 W (400 mW) × 25 s

•10 J = 0.0 W (placebo, 60 s)

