### Isokinetic protocol: eccentric contractions

Precisely 3 minutes after the end of LLLT, the volunteers will perform the eccentric contraction protocol, which will consist of 75 eccentric isokinetic contractions of the knee extensor musculature in the non-dominant leg (five sets of 15 repetitions, 30-second rest interval between sets) at a velocity of 60°.seg^-1^ in both the eccentric and concentric movements with a 60° range of motion (between 90° and 30° of knee flexion). At each contraction, the dynamometer will automatically (passively) position the knee at 30°; the dynamometer will then flex the knee until reaching 90°. The volunteers will be instructed to resist the knee flexion movement imposed by the dynamometer with maximum force. Instructions on how to execute the maneuver will be given first and the volunteers will receive verbal encouragement throughout the protocol. Despite the diversity of protocols proposed for the execution of eccentric exercises on isokinetic dynamometers, the protocol described here was chosen based on a previous study carried out [28] in which this method proved effective and reproducible for the exercise-induced muscle damage.

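### The laser section puts irradiation before the pre-exercise MVC while the abstract and MVC section put the MVC first; laser-first leaves active arms without a pre-laser reading of the primary outcome

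*Protocol article*

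**What the plan says.** The protocol article places the laser and the pre-exercise MVC in two different orders.

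- **Laser first.** *Variation of dose (phase 1)*: "LLLT will be applied 2 minutes prior to the pre-exercise MVC test".
- **MVC first.** Abstract, *Design and methods*: "The isokinetic test will be performed based on maximum voluntary contraction prior to the application of the laser".
- **MVC directly after warm-up.** *Isokinetic protocol: maximum voluntary contraction (MVC)*: "Immediately after the stretching and warm-up exercises, the maximum voluntary contraction (MVC) test will be performed". This section describes one pre-exercise MVC. All its other readings follow exercise, at 1 minute and 1, 24, 48, 72 and 96 hours.

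Three further statements bear on the timing.

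- *Stretching and warm-up* ends with pedalling "at 100 rpm for 5 minutes without load".
- *Isokinetic protocol: eccentric contractions*: "Precisely 3 minutes after the end of LLLT, the volunteers will perform the eccentric contraction protocol".
- *Variation of power (phase 2)* says that "the same methodological and evaluative measures will be employed", so the conflict carries into phase 2.

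*Data analysis* makes peak torque from the MVC the primary outcome, to be analysed by repeated-measures ANOVA over time with Bonferroni post hoc tests.

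**The concern.** A baseline should be measured before treatment. Under the order in the laser section, the only pre-exercise torque reading in the active arms comes after irradiation. Group D would also be read after its allocated procedure, but that is a sham, so its reading is unirradiated. The baseline would then carry any immediate effect of the laser on unfatigued muscle in three arms and not in the fourth.

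If the laser acutely raises torque, the group-by-time interaction and any change from baseline are pulled towards zero, and the group effect averaged over all time points is pushed up slightly. A baseline taken after the laser cannot be replaced later, and *Trial status* says recruitment was already under way at submission.

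Under the same order, the rest between warm-up and the baseline MVC would also differ by arm, because irradiation time differs by arm.

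**Working it through.** The plan gives no figure of its own on this point. The check is whether the statements can be reconciled, followed by what the laser-first order would do.

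**1. Can the orders be reconciled?**

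- *Laser before the warm-up.* The bike alone takes 5 min = 300 s. That exceeds the 120 s from laser to MVC and the 180 s from the end of the laser to the eccentric protocol, so this order fits neither interval.
- *Two pre-exercise MVCs.* The MVC section describes one, and the laser section refers to the test in the singular.
- *The 2 minutes counted from the start of the laser.* Irradiation lasts 180 s in Group B and 300 s in Group C. Both would still be under irradiation at the MVC, by 180 − 120 = 60 s and 300 − 120 = 180 s.

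So the laser-first order places the laser between warm-up and MVC, against both other sections.

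**2. Is laser-first feasible?** Yes. If the laser ends at 0 s, the MVC starts at 120 s and the eccentric protocol at 180 s. That leaves 60 s for three 5-second contractions (15 s). Staff could follow the sentence without meeting an obstacle.

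**3. Intervals by arm.** Irradiation times in phase 1 are stated. For phase 2 they are the 10 J example times the six sites: 100, 50, 25 and 60 s × 6 = 600, 300, 150 and 360 s. The 2 minutes are counted from the end of the laser. All values are minima, since no time is allowed for moving the probe.

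| Arm | Irradiation (s) | Laser-first: warm-up to MVC (+120 s) | MVC-first: MVC to exercise (+180 s) |
|---|---|---|---|
| Phase 1 A | 60 | 180 | 240 |
| Phase 1 B | 180 | 300 | 360 |
| Phase 1 C | 300 | 420 | 480 |
| Phase 1 D | 120 | 240 | 300 |
| Phase 2, 100 mW | 600 | 720 | 780 |
| Phase 2, 200 mW | 300 | 420 | 480 |
| Phase 2, 400 mW | 150 | 270 | 330 |
| Phase 2, 0 mW | 360 | 480 | 540 |

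The spread between arms is 420 − 180 = 240 s in phase 1 and 720 − 270 = 450 s in phase 2. It is the same size in either order; only its position changes.

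**4. Effect on the repeated-measures ANOVA.** Assume an active-minus-placebo difference of x at the pre-exercise reading and a constant d at the six later ones. Neither x nor d is in the documents.

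- Time-averaged group effect: (6d + x)/7, against 6d/7 when x = 0. The between-group sum of squares is multiplied by (1 + x/(6d))².
- Post-minus-pre contrast: d − x, against d.
- Interaction deviations: 6(x − d)/7 at the pre reading and (d − x)/7 at each of the six later ones. Their squares sum to (36 + 6)(d − x)²/49 = (6/7)(d − x)², so the interaction sum of squares is multiplied by (1 − x/d)².

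| x/d | Interaction multiplier | Between-group multiplier |
|---|---|---|
| 0 | 1.00 | 1.00 |
| 0.1 | 0.81 | 1.03 |
| 0.25 | 0.56 | 1.09 |
| 0.5 | 0.25 | 1.17 |
| 1 | 0 | 1.36 |

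The multipliers are the same with one active group or with three that share the same x and d.

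**The case against.** The best case against is that the harm needs two things at once: staff must follow the laser section rather than the other two, and the laser must act on unfatigued torque. The order of the methods sections (warm-up, MVC, laser, eccentric protocol) suggests that the laser sentence is the slip, in which case the intended baseline is clean. The Figure 1 flowchart, captioned as covering the "composition of groups and protocols in phases 1 and 2", may settle the order, but it is not shown here. *Data analysis* names no change-from-baseline endpoint, and direct comparisons of post-exercise torque are untouched. The multipliers rest on an assumed x and a constant d; a negative x would reverse both directions. The rest-time differences are not shown to alter torque.

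Most of this stands as a limit on the size of the problem. The bias is conditional, and the multipliers illustrate it without estimating it. The rest times describe the procedure and do not demonstrate harm. The DOMS baseline is also unaffected, since "Readings will be taken prior to stretching and warm-up".

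The contradiction itself remains. Figure 1 could show which order was meant, but it could not make the three sections agree. Because laser-first is feasible, the slip cannot be presumed: if that order was intended, the abstract and the MVC section are wrong and a pre-laser MVC is needed. The analysis is a repeated-measures ANOVA over time, so the interaction it can test is the quantity exposed.

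**Conclusion.** The concern holds. The text gives two incompatible orders for the laser and the only pre-exercise measurement of the primary outcome, in both phases. No reading of the stated timings reconciles them. That much is certain from the text.

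The consequence is conditional. If the laser section is followed, the active arms have no pre-laser peak torque. The loss in the interaction sum of squares is then nil at x = 0, 19% at x/d = 0.1 (1 − 0.81), 44% at 0.25 (1 − 0.56) and 75% at 0.5 (1 − 0.25). The between-group sum of squares rises by 3%, 9% and 17% at those last three ratios. These figures assume x is not negative, d is constant from 1 minute to 96 hours, and the active arms respond alike. Between-group comparisons of torque at 1 minute to 96 hours remain valid under either order. This should be fixed, but it does not invalidate the trial.

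**What to change.** Correct *Variation of dose (phase 1)* so that both phases follow one sequence: stretching and warm-up, pre-exercise MVC, laser, then the eccentric protocol 3 minutes after the laser ends. Check Figure 1 against it. Use only the pre-laser MVC as baseline. If an MVC after the laser and before exercise is also wanted, treat it as a post-treatment outcome.

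This equalises the rest before the baseline MVC. It does not equalise the interval from that MVC to exercise, which still varies with irradiation time (at least 240, 360, 480 and 300 s in phase 1 Groups A to D).

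The cost is a wording correction if MVC-first was intended. If laser-first was intended or has been practised, the procedure changes as well. Keeping a post-laser reading adds at most one three-contraction MVC per athlete.

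### The laser operator is said to be blinded, but every arm has its own application time, so an operator who knows the schedule can identify the arm

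*Protocol article*

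**What the plan says.** Under Composition of groups and randomization process, the protocol article has one researcher draw the allocation, program the device and keep the setting secret. It concludes: "Thus, the researcher in charge of the administration of the LLLT will be blinded to the dose and power applied to the volunteers". The device-level safeguard is given under Specifications: "To ensure blinding, the device will emit the same sounds regardless of the programmed mode (active or placebo".

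The application times are given under Variation of dose (phase 1). "In phase 1, the output power will be fixed at 200 mW", and six sites are treated. The entries for the four groups are:

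- Group A: "10 J on each application of the cluster with 200 mW (10 seconds of irradiation at each site"
- Group B: "30 J on each application of the cluster with 200 mW (30 seconds of irradiation at each site"
- Group C: "50 J on each application of the cluster with 200 mW (50 seconds of irradiation at each site"
- Group D (placebo): "0 J per diode (placebo) (20 seconds of irradiation at each site, 120 seconds of total time, but without effective irradiation"

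The phase 2 section, Variation of power, holds energy constant and varies power, and therefore time. Its worked example for 10 J gives 100, 50 and 25 s for 100, 200 and 400 mW, and for placebo "10 J = 0.0 W (placebo, 60 s".

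The primary outcome under Data analysis is peak torque from the maximum voluntary contraction (MVC). The MVC section says athletes are verbally encouraged during that test. The pain threshold is the pressure at which the athlete himself says it has become painful.

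**The concern.** The person holding the cluster on the skin at six sites cannot avoid noticing how long each application lasts. If duration differs between all arms, it acts as a label for the arm, and neither the identical sound nor the programming researcher's silence removes that label. The blinding statement and the application schedule are therefore incompatible as written.

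The two outcomes most open to expectation are peak torque, which depends on how hard the athlete tries and how he is encouraged, and the pressure pain threshold, which he declares. Bias in phase 1 would also carry forward, because the phase 1 result selects the dose used in phase 2. Blinding lost at application cannot be restored in the analysis.

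**Working it through.** **Inputs.** Energy per diode is 2, 6 or 10 J, power is 0.2 W per diode and there are six sites (Variation of dose). The relation is energy = power × time (Variation of power). The placebo times are assigned values: 20 s per site in phase 1 and 60 s in the 10 J example for phase 2. The latter is taken here as per site, like the active times beside it.

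**Phase 1, reproducing the plan's figures.** Time per site = energy ÷ power; total = 6 × time per site.

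| Arm | Time per site | Total |
|---|---|---|
| A, 2 J | 2 ÷ 0.2 = 10 s | 60 s |
| D, placebo | 20 s (assigned) | 120 s |
| B, 6 J | 6 ÷ 0.2 = 30 s | 180 s |
| C, 10 J | 10 ÷ 0.2 = 50 s | 300 s |

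All stated figures are reproduced. The four times are distinct, and neighbouring arms differ by at least 10 s per site and 60 s in total. At 0.2 W, 20 s would correspond to 0.2 × 20 = 4 J, which no active arm receives. For someone who knows the schedule, 20 s therefore means placebo. The largest difference in total time is 300 − 60 = 240 s.

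**Phase 2, for each dose that phase 1 could select.**

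| Dose | 100 mW | 200 mW | 400 mW | Active totals (× 6) | Largest active difference |
|---|---|---|---|---|---|
| 2 J | 20 s | 10 s | 5 s | 120, 60, 30 s | 90 s |
| 6 J | 60 s | 30 s | 15 s | 360, 180, 90 s | 270 s |
| 10 J | 100 s | 50 s | 25 s | 600, 300, 150 s | 450 s |

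In the 10 J example the placebo's 60 s matches no active arm, so all four times again differ. The article gives no placebo time for the other doses. If 60 s were kept at 6 J, placebo would coincide with the 100 mW arm and the other two arms would remain identifiable. The three active arms differ from one another at every dose.

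**Who is exposed.**

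- *Operator:* sees the duration directly. Identification follows if the operator knows the schedule, which is likely for a researcher on the trial but is not stated.
- *Athletes:* each feels only his own duration. All come from one team (Characterization of sample), so they can compare times.
- *Assessors:* the evaluator, the nurse taking blood and the algometer examiner are each stated to be blinded. The article does not say who gives the verbal encouragement, or whether that person sees the laser applied.

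**Timing relative to warm-up.** If warm-up precedes the laser, the time from warm-up to exercise also differs by arm: by up to 240 s in phase 1 and, among the active arms in phase 2, by 90, 270 or 450 s depending on the dose. The order is not settled. The MVC section puts that test straight after warm-up, Variation of dose puts the laser 2 minutes before the test, and the abstract puts the test before the laser.

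**The case against.** A reader might infer that athletes can identify their arm and that the whole double-blind claim therefore fails. The documents do not support that. Nothing says athletes are given the time-to-arm key, and dose and power are to be withheld from them. The placebo time is intermediate in both lists (20 s among 10, 30 and 50; 60 s among 25, 50 and 100), so it does not stand out as the sham. Teammates who compared notes would learn how their times rank, but not which one is inactive. Athlete unblinding is a possibility and no more.

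Blinding on the outcome side is also stated separately for the evaluator, the nurse and the algometer examiner. No text says that the operator tests or encourages athletes, so a route from operator to outcome is plausible but not shown. Serum markers are less open to this bias than torque or pain.

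A reader might also infer that dose is confounded with cooling or rest after warm-up. That depends on an order the article leaves inconsistent. The interval from end of laser to eccentric exercise is fixed at 3 minutes, and the document gives nothing to show that a few minutes before 75 eccentric contractions affects measurements out to 96 hours. The point stays conditional.

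Finally, the largest phase 2 figures apply only if 10 J is selected. These limits all stand. None of them reconciles the operator-blinding statement with the arm-specific times.

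**Conclusion.** The concern holds in a limited form. The statement that the laser operator is blinded is contradicted by the application times: four distinct times for four arms in phase 1, and again in the 10 J example for phase 2. This assumes only that the operator knows the schedule and can tell apart times that differ by at least 10 s per site, which is the smallest gap in either of those lists. Athlete unblinding is possible but uncertain, and the stated blinding of the assessors is not refuted. The direction and size of any bias in peak torque or pain threshold cannot be estimated from the document. The correction is still warranted, because a stated design property is not delivered, the primary outcome depends on effort, and the remedy is cheap.

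**What to change.** Reconcile Composition of groups and randomization process with the two sections that give application times. Leave every arm's energy, power and emission time as written. Within each phase, hold the cluster on each site for one common contact time in all four arms, for example the longest time programmed in that phase (50 s in phase 1; 100 s in phase 2 at 10 J). The non-emitting part must carry the same sound and display as the emitting part, since a silent period of arm-specific length would itself reveal the arm. Placing the non-emitting part first keeps the stated interval from end of laser to exercise unchanged.

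**Cost.** Per athlete, at most 300 − 60 = 240 s (4 minutes) more in phase 1, and 600 − 150 = 450 s (7.5 minutes) more in phase 2 at 10 J. The span from first to last emission lengthens in the shorter arms. In Group A it goes from 60 s to 10 + 5 × 50 = 260 s, ignoring repositioning. The device must be programmable in this way. That is assumed, as a researcher already programs it and a 0 mW mode with the same sound exists.

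**If the device cannot do this,** withdraw the claim that the operator is blinded, keep the operator away from testing and encouragement, and keep those who test and encourage away from the laser application. Matching placebo to one active arm would not be enough, because the active arms would still differ from one another.
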